### Validation data

Validation will be performed by local teams on 25% of data fields for 10% of cases. The validated fields will include key demographic and outcome data.

### Patient and Public Involvement (PPI) group

It will be possible to develop a PPI group of patients who have participated to the study. Towards the end of the study, the coordinator centre will invite a group of patients back to the hospital to discuss their personal opinion about the meaning of the research study.

### Ethics

The study was approved and registered by the University of Modena and Reggio Emilia Ethics Committee Area Vasta Nord Emilia-Romagna (Modena, Italy); approval number 448/2023/OSS/AOUMO–SIRER ID 6390, 14^th^ November 2023. The study was opened at each participating site. All participating units must obtain approval from their local Ethics Committee. It is the responsibility of the local study team to ensure that the ethical approvals are in place prior to commencing data collection. The principal investigators at each site will ensure that collaborators act in accordance with local clinical governance and guidelines.

The study has been externally peer reviewed by impartial professionals with relevant expertise (respiratory physicians, geriatricians, statisticians).

In the UK, this study was deemed to be a service evaluation, individually approved for use in the UK hospital site.

The study has been registered within www.clinicaltrials.gov: NCT05922202.

All the participants will provide written informed consent (S1 File).

### Status and timeline of the study

Recruitment of participants began on the 19^th^ December 2023 at the Hospital Policlinico in Modena (Italy) and will continue for two years (20^th^ December 2025).

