## Materials and methods

### Study summary

**Table 2** provides the summary of the study information.

**Table 2 pone.0300945.t002:** Study summary.

Study Title	Influence of frailty on cardiovascular events and mortality in patients with COPD
Study Design	Observational
Study Participants	COPD outpatients
Planned Size of Sample	320
Follow up duration	24 months
Planned Study Period	24 months
Research Question/Aim(s)	To assess frailty and number of cardiovascular events in adult patients with COPD in stable condition. To correlate frailty with long-term cardiovascular mortality, all-cause mortality, and mortality due to COPD in patients with COPD.
	The prevalence of frailty in COPD will also be measured.

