### Primary outcome

➢ Number of cardiovascular events (including hospital admissions due to cardiovascular cause) at 12 and 24 months in COPD patients living with frailty *vs* non-frail COPD patients.

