## Discussion

This protocol describes a study designed to investigate the influence of frailty on the risk of cardiovascular morbidity and mortality in patients with COPD. The study will also assess whether the frailty status can have an impact on all-cause mortality and death due to COPD.

This study will offer key real world data components to describe the complexity of COPD that is frequently associated with cardiovascular disease or other concomitant chronic diseases sharing common risk factors and playing a role in COPD prognosis. Additionally, patients with COPD have high risk of frailty that can increase their risk of mortality [7–12].

Relevant data collected includes comorbidities and GOLD grades based on the GOLD recommendations 2011 and 2023 (www.goldcopd.org) to characterise patient’s severity related to risk of exacerbation, hospitalisation, and death. The primary research questions this study will answer are whether the frailty status may be associated with the number of cardiovascular events and long-term cardiovascular mortality in a large, complete population with COPD. Answers to the questions of this longitudinal cohort study will inform chest physicians of the role of frailty in patients with COPD. More broadly, the clinical data collected in outpatient setting, including frailty, can have significant value to predict patient’s prognosis. This is a current topic in the field of respiratory research.

One limitation of the study design is the lack of a control group of individuals matched on age, sex, smoking habit, and frailty status, but without COPD. This would be useful to distinguish the potential role of COPD in the risk of development of cardiovascular disease [19].

All data will be reported as a whole cohort. Unit-level data for comparison will be fed back to collaborators to support local service improvement. This project will be submitted for presentation at a national or international Respiratory and Geriatric conference. Manuscript(s) will be prepared following close of the project. Manuscript(s) will also be prepared following interim data analysis at 12 months if numbers of patients recruited to the study at that time reach the planned sample size.

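### The 24-month planned study period cannot contain two years of recruitment plus 24 months of follow-up per patient (about 48 months), and the interim condition counts patients recruited, not patients followed for 12 months

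*Protocol article*

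**What the plan says.** The durations are spread over several sections of the protocol article.

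- *Study summary*, Table 2, has two separate rows: "Follow up duration 24 months" and "Planned Study Period 24 months". The table has no row for the length of recruitment.
- *Status and timeline of the study*: recruitment opened on 19 December 2023 at the Modena hospital and "will continue for two years", with 20 December 2025 as the end date.
- *Primary outcome*: "Number of cardiovascular events (including hospital admissions due to cardiovascular cause) at 12 and 24 months". *Secondary outcomes* sets the same two time points for cardiovascular, all-cause and COPD mortality, and *Follow up data* collects events and deaths at both.
- *Statistical analysis*: time to mortality starts at the individual's date of study entry.
- *Discussion*: manuscripts will follow the close of the project, which is not dated. They will also follow an "interim data analysis at 12 months if numbers of patients recruited to the study at that time reach the planned sample size".

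**The concern.** The stated study period equals the recruitment window, which leaves no time to follow patients who enter late. Those patients owe the study a further 24 months after recruitment stops. "Planned Study Period" is the only overall duration in the article, so it is the figure that a site, an ethics committee or a data manager would use to plan close-out. If it were used that way, the 24-month outcomes would be almost entirely unobserved, and many patients would lack the 1-year outcome on which the sample size rests.

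The interim sentence has a related weakness. Its condition is met by recruiting enough patients, whether or not anyone has been observed for 12 months.

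**Working it through.** **Inputs.** Recruitment runs from 19 December 2023 to 20 December 2025 (*Status and timeline of the study*). Follow-up is 24 months and the planned study period is 24 months (Table 2). The planned sample is 320 (Table 2; *Power and sample size*). No accrual rate is given, so every accrual pattern below is an assumption.

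**1. Recruitment window.** The two dates are 732 days apart, and 732 / 30.4375 = 24.05 months. The stated two years reproduces.

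**2. Total duration.** Minimum length = recruitment window + follow-up of the last patient = 24 + 24 = 48 months. A patient who enters on 20 December 2025 reaches 12 months on 20 December 2026 and 24 months on 20 December 2027, which is 48.03 months after the start. The stated 24 months does not reproduce as a total.

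**3. What each closing date would give.** With entry uniform over 0 to 24 months and closure at month C, follow-up is the smaller of C minus entry time and 24.

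| Closure (month) | Reach 12 months | Reach 24 months | Mean follow-up (months) |
|---|---|---|---|
| 24 | 50% | about 0% | 12 |
| 36 | 100% | 50% | 21 |
| 48 | 100% | 100% | 24 |

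In the first row, 0.50 × 320 = 160 patients would have the 12-month outcome. That share is the fraction who enter in the first half of the window, so it depends on the pattern. It is 1 − (1 − 0.5)² = 75% (240 patients) if accrual declines linearly to zero, and 0.5² = 25% (80 patients) if it rises linearly from zero. The near-zero share at 24 months holds under any pattern in which entry is spread over the window, because only patients who enter at the very start could reach it.

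**4. The interim, read as calendar month 12.**

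- *Would it fire?* At an even pace, 320 / 24 = 13.3 patients per month, so 12 × 13.3 = 160 are enrolled at month 12 and the condition fails. Reaching 320 by then needs 320 / 12 = 26.7 per month, twice that pace.
- *If it fires*, all 320 entered within the preceding 12 months, so essentially none has completed 12 months. Mean follow-up = 12 − mean entry time:

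| Accrual of the 320 | Mean entry (month) | Mean follow-up (months) |
|---|---|---|
| Uniform over 12 months | 6 | 6 |
| Linearly declining over 12 months | 4 | 8 |
| Linearly rising over 12 months | 8 | 4 |
| Uniform over the first 6 months | 3 | 9 |

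Steps 3 and 4 use different accrual assumptions and cannot both describe one study. With 320 spread evenly over 24 months, the interim does not happen.

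**5. Sample size.** At two-sided 0.025 and 80% power, 40% versus 60% needs 118 per group against the planned 120 (power 0.809 at 120:120). For 40% versus 75% at 120:80, power is 0.998. The figure of 320 reproduces, and the duration conflict does not alter it.

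**The case against.** The strongest reply is that this is a labelling problem. Table 2 keeps follow-up and study period on separate rows, and the recruitment window is also 24 months, so the second row may simply mean the enrolment period. That reading removes the conflict, but the article does not state it. If it is what was meant, the row is mislabelled and the total length appears nowhere.

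A reader might infer that data will actually close at month 24 and that half of the 12-month outcomes will be lost. The article does not support that. It gives no date for closing the data, it sets outcomes at 12 and 24 months, and it counts mortality time from each patient's entry. All of this points to an intention to follow everyone for 24 months. The figures for closure at month 24 show what the stated period would do if applied as the total; they do not predict what will happen. Even then, the Cox analyses would use the censored time of patients with short follow-up. Frailty prevalence, also a secondary outcome, has no 12- or 24-month time point.

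A reader might also infer that the interim will analyse patients with about 6 months of follow-up. That too goes beyond the text. The interim is conditional and fails at an even two-year pace, and 6 months is a mean under one accrual pattern. Elsewhere in the article 12 months refers to patient follow-up, so the sentence is ambiguous, although its wording about numbers recruited at that time favours calendar time. Nor does the article say what the interim manuscript would report. What stands is narrower: on either reading, the condition as written does not require completed 12-month follow-up.

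**Conclusion.** The point holds in two parts of different strength.

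The duration conflict needs no assumption about accrual. As a total, 24 months is wrong by about 24 months: the article's own recruitment dates and follow-up require about 48, ending around December 2027.

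The interim condition is badly fixed, but its effect is conditional. On the calendar reading, and only if recruitment runs at about twice the even pace, the analysis would take place with essentially no patient at 12 months. Mean follow-up would then be 6 months under uniform accrual and about 4 to 9 months across the patterns tried.

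The sample size is unaffected. What is at stake is when data close and which patients contribute to the 12- and 24-month results.

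**What to change.** 1. In Table 2, either restate the total study period as about 48 months, or relabel the 24 months as the recruitment window and add a row for the total. *Status and timeline of the study* should agree and give the expected last 24-month assessment, about December 2027.
2. In the Discussion, replace the recruitment-count condition. The 12-month analysis should take place when all patients of the planned sample have completed 12 months, died, withdrawn or been lost to follow-up. If recruitment runs to its stated end, this is about December 2026 at the latest. Withdrawal and loss must be named: if exactly 320 are recruited, a condition met only by completion or death could fail because of one lost patient.
3. Time the final analysis by the same condition at 24 months.

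The text change is small: one table entry, the timing sentence and a line on the final analysis. The real cost is later reporting, with 12-month results waiting for follow-up to mature and 24-month results not due until about December 2027.

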## Discussion

This protocol describes a study designed to investigate the influence of frailty on the risk of cardiovascular morbidity and mortality in patients with COPD. The study will also assess whether the frailty status can have an impact on all-cause mortality and death due to COPD.

This study will offer key real world data components to describe the complexity of COPD that is frequently associated with cardiovascular disease or other concomitant chronic diseases sharing common risk factors and playing a role in COPD prognosis. Additionally, patients with COPD have high risk of frailty that can increase their risk of mortality [7–12].

Relevant data collected includes comorbidities and GOLD grades based on the GOLD recommendations 2011 and 2023 (www.goldcopd.org) to characterise patient’s severity related to risk of exacerbation, hospitalisation, and death. The primary research questions this study will answer are whether the frailty status may be associated with the number of cardiovascular events and long-term cardiovascular mortality in a large, complete population with COPD. Answers to the questions of this longitudinal cohort study will inform chest physicians of the role of frailty in patients with COPD. More broadly, the clinical data collected in outpatient setting, including frailty, can have significant value to predict patient’s prognosis. This is a current topic in the field of respiratory research.

One limitation of the study design is the lack of a control group of individuals matched on age, sex, smoking habit, and frailty status, but without COPD. This would be useful to distinguish the potential role of COPD in the risk of development of cardiovascular disease [19].

All data will be reported as a whole cohort. Unit-level data for comparison will be fed back to collaborators to support local service improvement. This project will be submitted for presentation at a national or international Respiratory and Geriatric conference. Manuscript(s) will be prepared following close of the project. Manuscript(s) will also be prepared following interim data analysis at 12 months if numbers of patients recruited to the study at that time reach the planned sample size.
